### Data management

Emerging innovative information technologies, such as data management system software packages, can assist disease control programmes to better manage and analyse data, and thus make it easier to carry out routine surveillance, monitor interventions, and evaluate control programme performance. This will lead to better informed decision making and actions on the part of health authorities. The Liverpool School of Tropical Medicine have developed a multi-disease data management system (DDMS+) platform that facilitates the real-time monitoring and evaluation of interventions that are essential for understanding the progress, success, and challenges facing disease control operations [39]. DDMS+ is an open source data management software program that works as a modular, integrated system. Currently, DDMS+ has been successfully trialled for other vector-borne diseases in eight countries for malaria and one for leishmaniasis. The DDMS+ will be implemented for the dengue study and bring this state-of-the-art technology to the Philippines Department of Health through training exercises and workshops.

### Statistical analyses

#### Classification of dengue incidence as ‘hot’, ‘intermediate’, and ‘cold’ spots

Dengue incidence for the previous 5 years will be acquired at the *purok* level, and the midpoint of the *purok* used as the geographical coordinate representing the *purok*. Population density at the *barangay* level will be acquired. Hot/coldspot classification of dengue incidence rate will be achieved through analysis using Kulldorff’s scan statistic in SaTScan™ (version 9.1.1) (http://www.satscan.org/) [40]. A discrete Poisson model will be used to analyse the spatial distribution of dengue cases using all 5 years of incidence data, with year as the analysis time unit and population density as a covariate. Within SaTScan™, an infinite number of cluster circles are generated with a minimum size diameter set to 300 m, the approximate size of the future clusters. A maximum value will initially be set to 1 km and then altered as a function of the number and type (hot/cold) of clusters detected. SaTScan™ identifies hot or cold spots that represent either more or less than the expected dengue cases compared with the entire study area. SaTScan™ then calculates the relative risk of observed hot and coldspots, and statistical significance of these spots is determined using a likelihood ratio test. Only spots with no geographical overlap will be accepted. Areas that are neither hotspots nor coldspots will be classified as intermediate. Hot and cold spots will contain a variable number of *purok*s and it is possible, and indeed likely, that hot and cold spots vary year to year. Therefore, *purok*s will be classified by annual similarity, in other words year 1 in hotspot, year 2 not, year 3 coldspot, and so on. In this way *purok*s can be classified into a risk designation and matched for treatment and control site selection.

#### Sero-conversion

Sero-conversion of individuals to DENV will be analysed yearly using three saliva samples taken from each individual during each year (six total samples per volunteer). Because there are repeated measures from the same individual, sero-conversion is analysed using a generalised linear mixed model (GLMM) with ‘individual’ as a random factor. We will also include cluster ID, school, and occurrence (yes/no) of any public health mosquito control intervention performed in the cluster, and when, as random factors. Sero-conversion will be considered both as 1) a four-fold titre rise in DENV IgG optical density (OD) from baseline to post-treatment (year 1 or 2) samples, thus classifying individuals into yes/no (Y/N) sero-conversion, and 2) the actual change in OD without the restrictive definition of a four-fold increase. This double analysis will enable assessment of change in IgG OD beyond that using the classical threshold of an arbitrary four-fold increase. The Y/N IgG OD analysis will use logistic regression and the latter OD measure log-linear regression. Time (Post1 and Post2 for Y/N logistic regression; Pre-, Post1, and Post2 for log-linear regression), treatment (intervention Y/N), age (continuous), sex (male/female), vaccination status (0, 1, 2, 3 inoculation categories), and site (*purok*) risk (baseline seropositive prevalence rate) will be the explanatory variables. All analyses will be performed using Genstat version 15 [41].

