### Sample size calculations

The sample size is calculated using the following standard formula when considering proportions (incidence rate):$$ n=2{\left(\mathrm{Za}+\mathrm{Z}1-\upbeta \right)}^2\ \mathrm{p}\left(1-\mathrm{p}\right)/{\left(\mathrm{p}0-\mathrm{p}1\right)}^2 $$

Where *n* is the required sample size per treatment arm (control or treatment), Zα and Z1–β are constants set by convention according to the accepted α error and whether a one-sided or two-sided effect, p0 is the proportion infected in control areas, and p1 the proportion infected in treatment areas (p = (p0+p1)/2).

Assuming a *p* < 0.05 as acceptable and a study with 90% power, the following constant values are: Zα = 1.96 (two-tailed); Z1–β = 1.2816.

The final sample size will depend on the dengue transmission rate in the study areas as estimated from the historical mean rate. Recent sero-conversion studies in Cebu City, Philippines, have observed a symptomatic incidence rate of 1.6 per 100 person-years (1.6%) with 7% subclinical infections in the general population, increasing to 7% symptomatic cases and 17% subclinical infections in children < 15 years old [34]. Historical annual incidence rates were estimated at between 11 and 22% [35]. Reported incidence rates in our study area (under administrative Region IV-A) are consistently amongst the highest in the country. To be conservative, however, we estimate an infection incidence of 3% (to include symptomatic and subclinical infections). For an efficacy of treatment of 50% (i.e. reduction in dengue), with 90% power, a minimum of 2054 children (aged 6–16 years old) will need to be recruited in treatment sites with an equivalent number in matched control sites and followed for 2 years. We factor in a drop-out of 250 children (~ 12.2%) per treatment and control arm (500 total) over the 2-year period. Thus, the total number of children to be recruited is 4600, distributed over 46 clusters of 100 children each.

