### Outcomes

The principle evaluation criterion is the epidemiological efficacy read out: dengue infection sero-conversion. Sero-conversion to dengue virus exposure will be measured by an enzyme-linked immunosorbent assay (ELISA) for immunoglobulin (Ig)G titres using repeated saliva samples taken sequentially during three cross-sectional studies at months 0, 3 (end of month 2), and 5 (end of month 4) during the intervention (In2Care® trap placement) period each year in both treatment and control sites. These time points are designated Pre-, Post1, and Post2 within each year.

The secondary evaluation criterion is the entomological read out. To measure the impact of the In2Care® traps on the adult mosquito population densities, 20 GATs will be placed in each of 10 randomly selected treatment and 10 control sites matched with intervention sites for historical dengue incidence. *Aedes* spp. (both *Ae. aegypti* and *Ae. albopictus*) adults will be counted and identified in the GATs once each week beginning 2 weeks before intervention, throughout the intervention period, and 2 weeks post-intervention. Traps will be placed both inside and outside 10 randomly selected houses within each site. Traps placed outside will be positioned against the wall of the house in an area with shelter from direct sunlight. Traps placed inside the house will be positioned in a suitably unobstructed area but where there is air movement.

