### Saliva sampling and biological analyses

A saliva sample will be taken by spitting into a sterile urine collection container, kept on ice, and transported to RITM for further processing. A 1-mL aliquot will be placed in a labelled Eppendorf® tube for storage at −20 °C. Sampling will occur just prior to, during (after 2 months of trap deployment), and at the end of the 4-month intervention period for 2 successive years. Sero-conversion testing will be performed using an in-house ELISA developed by Institut Pasteur [38] in duplicate on “paired” pre-/concurrent/post-samples from the same individual for each season. Although IgM titres will rise during a secondary DENV infection, a significant increase in IgM titres only systematically occurs in primary dengue infections and is relatively short lived; therefore, changes in IgG titres will be measured [38]. Exposure to dengue virus will produce an increase in IgG titre compared with the baseline titre in an individual, irrespective of whether they have been vaccinated or not or having been previously exposed to any DENV serotype (See Statistical analyses below). The technicians performing the ELISAs will have no prior knowledge whether the samples come from a treatment or control site. Upon study completion, analyses, and publication, all saliva samples will be destroyed and coding files erased.

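### The yes/no sero-conversion rule asks for a four-fold rise in optical density, while other sections describe titres; taken literally, it misclassifies children with high or near-blank baselines

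*Protocol article*

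**What the plan says.** Under Outcomes, the principal criterion is sero-conversion, "measured by an enzyme-linked immunosorbent assay (ELISA) for immunoglobulin (Ig)G titres using repeated saliva samples". Saliva sampling and biological analyses also works in titres: "Exposure to dengue virus will produce an increase in IgG titre compared with the baseline titre in an individual", and this is said to hold "irrespective of whether they have been vaccinated or not or having been previously exposed to any DENV serotype". Specific data collection records ELISA titres for each child.

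The Sero-conversion section changes scale. Its first definition is "a four-fold titre rise in DENV IgG optical density (OD) from baseline to post-treatment (year 1 or 2) samples". Its second is "the actual change in OD without the restrictive definition of a four-fold increase", added so that change can be assessed "beyond that using the classical threshold of an arbitrary four-fold increase". On the models it says: "The Y/N IgG OD analysis will use logistic regression and the latter OD measure log-linear regression". The section names no conversion from OD to titre and does not require the post sample to be positive.

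Sample size calculations compares two proportions, 3% in control and half of that under treatment. That corresponds to the yes/no definition.

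**The concern.** A four-fold rule suits a dilution titre, which can go up four-fold from any starting level. OD has a floor at the blank and a ceiling at the reader maximum, and it is not proportional to antibody near either end. Applied to OD, the rule fails in two ways:

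- **Ceiling.** A child who starts high, through past infection or vaccination, may have no room for a four-fold rise however strong the response. Such infections are missed.
- **Floor.** A child who starts near blank can quadruple through measurement error and still be negative. Such children are counted as infected.

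Missed infections reduce events and power. False conversions occur at about the same rate in both arms, so they pull the estimated efficacy towards zero. That pull is strong when the true risks are only 3% and 1.5%. A trap that really halves infection could be reported as having a smaller effect, or none.

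**Working it through.** **1. The plan's own figure.** Inputs from Sample size calculations: p0 = 0.03, 50% efficacy so p1 = 0.015, mean p = 0.0225, Zα = 1.96, Z1–β = 1.2816.

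n = 2 × (1.96 + 1.2816)² × 0.0225 × 0.9775 / 0.015² = 2054.3. The stated 2054 per arm reproduces. It gives 90% power only if every infection is detected and no uninfected child is counted.

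**2. Ceiling.** If the reader maximum is M, a four-fold rise needs a baseline of at most M/4. The article does not give M. For assumed values of 2, 3 and 4, baselines above 0.50, 0.75 and 1.00 cannot qualify.

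**3. Floor.** Assume no true change, true OD μ, independent normal error with SD σ per well, and duplicates averaged (the article specifies duplicates). Then post − 4 × pre has mean −3μ and variance 17σ²/2. The chance of an apparent four-fold rise at one post sample, by simulation with readings floored at 0.001, is:

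- σ = 0.02: 14.3% at μ = 0.02, 6.1% at 0.03, 0.5% at 0.05, about 0 at 0.10 and above.
- σ = 0.01: 2.0% at μ = 0.02, 0.1% at 0.03, about 0 at 0.05 and above.

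Both σ and μ are assumptions. The problem is confined to readings very close to blank, but there the false rate can equal or exceed the 1.5% to 3% under comparison.

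**4. Effect on power.** With sensitivity Se and specificity Sp, the observed risk is p × Se + (1 − p) × (1 − Sp). Putting the observed risks q0 and q1, with mean q, into the plan's formula at n = 2054 gives power = Φ(√[n(q0 − q1)² / (2q(1 − q))] − 1.96). Clustering is ignored, as in the plan's formula.

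| Se | Sp | Observed risks | Apparent efficacy | Power |
|---|---|---|---|---|
| 1.0 | 1.00 | 3.00% v 1.50% | 50% | 0.900 |
| 0.7 | 1.00 | 2.10% v 1.05% | 50% | 0.771 |
| 1.0 | 0.99 | 3.97% v 2.485% | 37% | 0.768 |
| 1.0 | 0.98 | 4.94% v 3.47% | 30% | 0.651 |
| 0.8 | 0.99 | 3.37% v 2.185% | 35% | 0.637 |

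The second row in full: mean 0.01575; 2054 × 0.0105² / (2 × 0.01575 × 0.98425) = 7.30; √7.30 − 1.96 = 0.74; Φ(0.74) = 0.77.

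**5. How many children might start high.** The article gives no OD distribution, so past infection is only a rough guide. At a constant 3% a year, past infection by age 11 (the middle of 6 to 16) is 1 − 0.97¹¹ = 28%. If every such child were above the ceiling and infections fell evenly, sensitivity would be about 72% and power about 78%. Vaccinated children would add to the high-baseline group by an unknown amount.

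**The case against.** The strongest reply is that use of raw OD is inferred. Several sections say titre, and so does the disputed sentence itself. The assay is an in-house method described in a cited source, and plate-level detail is normally left out of an article. If true titres or calibrated units are used, the objection falls away. This stands as a limit on the finding. It does not remove it, because the article states the endpoint rule on OD and names the model as an OD analysis.

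The plan also sees the weakness. It calls the threshold arbitrary and adds a threshold-free definition that can register smaller rises. This is real mitigation. But OD change is compressed near saturation too, and the sample size rests on the yes/no form.

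Three stronger readings are tempting, and the article does not support them:

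- **A contradiction with the saliva sampling section.** A reader might set the rule against the statement that exposure raises IgG whatever the child's history. That statement promises an increase, not a four-fold one.
- **Most children being unable to convert.** "Historical annual incidence rates were estimated at between 11 and 22"% would imply 1 − 0.89¹¹ = 72% to 1 − 0.78¹¹ = 93% past infection at age 11. But those rates follow the Cebu City data and are not given for Lipa City, and having been infected is not the same as being above the ceiling. It also mixes scenarios to pair them with power losses computed at 3%. If 11% also held during the trial, power at 2054 per arm would be 99% even at 50% sensitivity, before clustering.
- **Serious depletion in year 2.** Removing year-1 converters moves a true risk ratio of 0.50 only to 0.50 × 0.985/0.97 = 0.508. A season-specific baseline is in any case already indicated, since Outcomes labels Pre, Post1 and Post2 within each year.

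**Conclusion.** The point holds in a limited form. The article states a four-fold rule on OD in one section and describes titres in others, and these must be reconciled. Followed as written, the rule cannot class some high-baseline children as converters and can class some negative children as converters.

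The ceiling and floor follow from OD being bounded, but their size cannot be derived from the article. Reader maximum, noise, sensitivity and specificity are all assumed above. A fall in power from 90% to about 77%, or in apparent efficacy from 50% to about 37%, shows what modest misclassification would do. It is not a forecast.

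Misclassification equal in both arms mainly costs power and biases towards no effect; it need not inflate type I error. A chance imbalance in baseline antibody between arms could add some bias. The change should be made before any sample is classified.

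**What to change.** 1. State in the Sero-conversion section that the four-fold rule applies to titre or standard-curve units, not raw OD, and align Outcomes, Saliva sampling and Specific data collection with it. If the assay already yields such units, this is a wording change only. If not, it needs a standard dilution series on each plate and diluted re-runs of samples above the linear range. Aliquots are stored at −20 °C, so this is feasible where volume allows and before they are destroyed.
2. Require the post sample to be above the assay's positivity cut-off. Such a cut-off must already exist: the benefits section promises to tell families whether a child is sero-positive, and the model uses baseline seropositive prevalence. This costs nothing.
3. Add each child's log Pre value for that season as a covariate in the yes/no model. It does not correct misclassification, but it accounts for conversion depending on baseline and for imbalance between arms. It uses data already collected. It should stay out of the log-linear model, where Pre is already one of the response times.

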#### Adult mosquito spatial distributions (relative densities) using GATs

Weekly adult mosquito catches will be analysed by fitting a GLMM with the response variable as mosquitoes/trap/week, time (week), and intervention (Y/N) as fixed effects, and cluster ID and cluster risk designation as random effects. In addition, we will include occurrence of any public health mosquito control intervention performed in the cluster by counting the numbers of days during the 2 month inter-saliva sampling period when mosquito numbers could have been affected by such a control intervention (up to 14 days maximum post-control) as a random factor. We will test for over-dispersion in the response variable and, if it exists, an over-dispersion parameter will be estimated and applied. Otherwise, a Poisson distribution will be assumed. Two models will be constructed, one for each *Aedes* dengue vector species.

Additionally, a second series of analyses involving the distance of GATs from the nearest In2Care® trap will be analysed using log-linear regression, fitting the actual Euclidean distance in metres as a continuous variable. Because the extent to which an area is built up can impede mosquito flight (i.e. barriers), each cluster will be categorised into an urban typology (categorical building density) and this will be fitted as a factor in the analyses.

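### The OD model keeps the pre-deployment visit as a time level but lists no treatment-by-time term, so an arm-coded treatment coefficient recovers only two thirds of the effect

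*Protocol article*

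**What the plan says.** All references are to the Protocol article.

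- **Response (Sero-conversion).** The second of two analyses takes "the actual change in OD without the restrictive definition of a four-fold increase".
- **Time and treatment (Sero-conversion).** Time in the Y/N model is Post1 and Post2; for the OD model the list runs "Pre-, Post1, and Post2 for log-linear regression), treatment (intervention Y/N), age (continuous), sex (male/female"). The Y/N model therefore uses post visits only, while the OD model keeps Pre.
- **Rest of the list (Sero-conversion).** After age and sex come "vaccination status (0, 1, 2, 3 inoculation categories), and site (*purok*) risk (baseline seropositive prevalence rate) will be the explanatory variables". Neither an interaction nor the child's own baseline OD appears.
- **Random factors (Sero-conversion).** Individual is one, and "We will also include cluster ID, school, and occurrence (yes/no) of any public health mosquito control intervention performed in the cluster" adds the others.
- **Timing of Pre (Saliva sampling and biological analyses).** "Sampling will occur just prior to, during (after 2 months of trap deployment), and at the end of the 4-month intervention period". In year 1, Pre is thus an untreated visit.
- **Mosquito catches.** The GAT model has "time (week), and intervention (Y/N) as fixed effects" (Adult mosquito spatial distributions). Counts are taken "once each week beginning 2 weeks before intervention, throughout the intervention period, and 2 weeks post-intervention" (Outcomes). Neither an interaction nor a baseline catch is listed.

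**The concern.** The trap effect on OD is the arm difference in movement away from Pre. A model with three visits and one arm term estimates something else: the arm difference averaged over all visits, including one at which the traps cannot yet have acted. Random intercepts for child and cluster do not repair this, because arm is constant within both.

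Two things are at stake. The reported effect is too small by a fixed factor. And, depending on what the response is, baseline differences between children and between clusters may stay in the contrast. The OD analysis is one of two named analyses of the principal criterion, and was added to see effects that a four-fold cut-off misses, so a loss of sensitivity defeats its purpose.

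**Working it through.** **The plan's own figure.** The article gives no figure for the OD or GAT models. Its sample size does reproduce: p = (0.03 + 0.015)/2 = 0.0225, and 2(1.96 + 1.2816)² × 0.0225 × 0.9775/0.015² = 2054.3, stated as 2054 per arm. The 3% and 1.5% are reused in step 4.

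**Step 1. Raw OD response, treatment coded as arm.** Let b be a chance arm difference at Pre, and d1, d2 the effects at Post1 and Post2. In a balanced design the coefficient is the mean of the three arm differences:

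[b + (b + d1) + (b + d2)]/3 = b + (d1 + d2)/3

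- d1 = d2 = d: b + (2/3)d.
- d1 = d/2, d2 = d: b + 0.5d, where the mean post effect is 0.75d. The ratio is again 2/3.
- No effect, b = 0.3: 0.300.

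A generalised least squares calculation with 23 clusters per arm and random intercepts for cluster and child gave 0.667 (d = 1, b = 0), 0.500 (effects 0.5 and 1) and 0.300 (no effect, b = 0.3). The treatment-by-time contrasts were 1 and 1, 0.5 and 1, and 0 and 0.

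**Step 2. Change from Pre as response.** The Pre rows are zero by construction. The coefficient is (0 + d1 + d2)/3: b has gone, and the factor 2/3 remains.

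**Step 3. Intervention coded N for everyone before deployment.** With d = 1 and b = 0 the coefficient is 1.00. With no effect and b = 0.3 it is 0.0435, so 0.0435/0.3 = 14.5% of b is left (20 children per cluster, ICC 0.02, within-child correlation 0.8). This coding largely removes the problem.

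**Step 4. Scale, raw OD response.** Assumptions, none given in the article: every infection produces exactly a four-fold rise; SD of log OD 0.5–1.0; ICC 0.01–0.05; within-child correlation 0.8; no cluster-by-time variance. There are 100 children per cluster.

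- Mean effect: ln 4 × (0.03 − 0.015) = 0.0208. After dilution: 0.0208 × 2/3 = 0.0139.
- SD of b: SD × √{2[ICC + (1 − ICC)/100]/23} = 0.021 to 0.072, which is 1.0 to 3.5 times the mean effect.

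| SD of log OD | ICC | As listed: effect/SE (SD units) | Power | Treatment on after Pre: effect/SE | Power |
|---|---|---|---|---|---|
| 0.5 | 0.01 | 0.0277/0.0402 | 11% | 0.0416/0.0156 | 76% |
| 0.5 | 0.05 | 0.0277/0.0711 | 7% | 0.0416/0.0160 | 74% |
| 1.0 | 0.01 | 0.0139/0.0402 | 6% | 0.0208/0.0156 | 27% |
| 1.0 | 0.05 | 0.0139/0.0711 | 5% | 0.0208/0.0160 | 26% |

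**Step 5. Dependence on the response and on cluster-by-time variance.** Second assumed set: (4600 − 500)/46 ≈ 89 children per cluster, total variance 1, within-child correlation 0.7, cluster variance 0.03, cluster-by-time variance 0.002, effects 0.04 and 0.08 SD.

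- Variance of a cluster mean: v = 0.03 + 0.002 + (0.67 + 0.298)/89 = 0.0429. Covariance across visits: c = 0.03 + 0.67/89 = 0.0375.
- As listed, raw OD: effect 0.04, SE = √[(2/23)(3v + 6c)/9] = 0.0585, power about 10%.
- Post mean adjusted for Pre: effect 0.06, SE = √{(2/23)[(v + c)/2 − c²/v]} = 0.0253, power 66%.
- Change from Pre: effect 0.06, SE = √[(2/23) × 1.5(v − c)] = 0.0264, power 62%. Adding zero Pre rows multiplies effect and SE alike by 2/3, so power stays at 62%.
- Cluster-by-time variance of 0.010 or 0.020: adjusted power falls to about 35% or 24%; as listed it stays near 10%.

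**Step 6. GATs.** Four months is about 17 weeks, so the window is 2 + 17 + 2 = 21 weeks. Assume equal expected catches each week without traps, and that all weeks enter the model. A true rate ratio of 0.50 reads as (2 + 19 × 0.5)/21 = 0.55 if only the 2 pre weeks are unaffected. It reads as (4 + 17 × 0.5)/21 = 0.60 if the effect also ends at trap removal. A true 0.70 reads as 0.73 or 0.76.

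**The case against.** The strongest reply is that the article does not commit to the damaging model.

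- **Response.** The outcome is called a change in OD. On that reading baseline imbalance cancels and power is 62% against 66% (step 5). This stands, and it removes most of the power argument. It does not remove the 2/3 scaling, and a change score sits badly with a Pre level of time.
- **Coding.** One might argue that the companion Y/N model forces arm coding. It does not: that model has only post visits, where arm coding and on-after-deployment coding are identical. The coding is therefore open, and the text does not give the one that largely works.
- **Condensed article.** A full analysis plan might add an interaction. But the article names the response, time levels, covariates and random factors, and says these will be the explanatory variables. Followed as listed, with arm-coded treatment, the model is mis-targeted.
- **Existing safeguards.** Matching and the site-risk covariate reduce imbalance between sites. They do not remove differences in individual baseline OD, and the step 4 figures give them no credit.
- **GATs.** The article gives the collection window but does not say which weeks enter the model. The dilution is mild even if all do.

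**Conclusion.** The point holds as a defect of specification in the OD model. With arm-coded treatment the coefficient is two thirds of the mean post-deployment effect, whether the response is OD or change in OD. If the response is OD itself, a chance Pre difference is added at full weight and precision is lost. Only coding intervention as N before deployment largely avoids this, and it is not stated.

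The loss of power is illustrative: about 5–11% against roughly 25–75% for a raw OD response under the assumptions of step 4, and little loss if the response is change. A reader might infer a fixed collapse such as 10% against 66%. The documents do not support that, because it requires a raw OD response and a small cluster-by-time variance that they do not give.

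A reader might also infer that the main sero-conversion result is compromised, or that false positives are inflated. Neither follows. The four-fold Y/N analysis uses post visits measured against each child's own baseline and is not affected. With randomisation and clustering modelled, type I error is kept; the cost is attenuation, lost precision and bias conditional on the imbalance seen. The GAT issue is the same in kind and milder: 2 to 4 of about 21 weeks.

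**What to change.** **OD.** State the response as log OD at Post1 and Post2. Use the child's year-1 Pre log OD as covariate, with treatment, time, treatment-by-time, the listed covariates, and random effects for cluster and child. Name the Post1 and Post2 treatment contrasts as the effect. Alternatively, keep Pre in the model and take the treatment-by-time contrasts. Either way, state how intervention is coded at each visit.

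**Year 2.** Year-2 Pre follows the year-1 intervention. Do not assume equal arm means there or treat it as an untreated baseline, because adjusting for it could remove a carried-over effect. Use the year-1 Pre value as the baseline in both years, and report change within year 2 separately.

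**GATs.** Estimate the effect on the intervention weeks, with the cluster's year-1 pre-intervention catch as covariate. Report the post-removal weeks separately.

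**Cost.** Wording of the analysis only. The year-1 Pre saliva samples and pre-intervention catches are already planned.
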